### Specimen preparation and lesion formation

One hundred and fifty-five permanent bovine central and lateral incisors were obtained from newly slaughtered cattle (Figure 4a). The bulk of the adherent soft tissues was carefully removed using scalpels (disposable scalpel; Feather, Osaka, Japan), and the teeth were stored in 0.9% sodium chloride solution until further processing (Fresenius; Bad Homburg, Germany). Two enamel specimens (4 × 4 × 3 mm^³^) were prepared from the labial aspect of each crown under running tap water using a diamond-coated band saw (Exakt 300cl; EXAKT Apparatebau, Norderstedt, Germany). Two dentin specimens were prepared from the cervical regions: one specimen from the oral and one from the buccal aspect (Figure 4a). Enamel and dentin surfaces were ground flat and polished progressively up to 4,000 grit (silicon carbide abrasive paper; Hermes, Hamburg, Germany; Figure 4a). The surfaces were examined under a stereomicroscope (Axioplan 2; Carl Zeiss, Göttingen, Germany) with a magnification factor of 10 to ensure absence of any defects or physical damage. One enamel specimen from each incisor was then embedded in epoxy resin (Technovit 4071; Heraeus Kulzer, Wehrheim, Germany; Figure 4b), while the natural surface was kept free from resin. The flat parts of the specimens were ground and polished up to 4,000 grit (silicon carbide; Struers, Ballerup, Denmark), thereby removing the outer parts of the enamel (approximately 200 μm).

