If one specimen demonstrated surface erosions after *in situ *exposure, an adjacent sound part of the specimen was used for microradiography to permit adjustment of the starting point. Mineral loss and lesion depth at the specimens' surfaces were determined separately for each test field (Figure 3). Mineral losses in sound areas (ΔZ_Sound_; S in Figure 3) were subtracted from the respective values determined for artificially demineralized areas (ΔZ_Demin_; D in Figure 3b) and from the areas that were exposed to saliva substitutes for either five (ΔZ_Effect 1_) or seven weeks (ΔZ_Effect 2_) [33,34]. In artificially demineralized specimens, the values of the demineralized fields were subtracted from those obtained for the particular effect fields (E1 and E2 in Figure 3). Changes in mineral loss (ΔΔZ_Effect 1 _= ΔZ_Demin _- ΔZ_Effect 1_; ΔΔZ_Effect 2 _= ΔZ_Demin _- ΔZ_Effect 2_) were also determined. Positive and negative ΔΔZ values indicated remineralization and demineralization, respectively. Lesion depths were determined using analogous methods.

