### Statistical analyses

Sample size was calculated using nQuery (version 3.0; Statistical Solutions, Cork, Ireland) prior to the start of this *in situ *study. To determine an appropriate specimen quantity to achieve an adequate power of 80% and a defined significance level of 5% (p < 0.05), the number of participants was determined to be 38 (in anticipation of a dropout rate of 10%). The expected mean value of mineral loss was 200 vol% × μm with a standard deviation of 400 vol% × μm. These values were calculated taking into account the ascertained values of previous *in vitro *studies [27,33]. In detail, those studies gave informations about the required contact time between specimens surface and saliva substitute *in vitro*, thus these results served as base for determining the specimens *in situ *contact time storage. After transversal microradiography evaluation and collection of the questionnaires, statistical analyses will be conducted using a *t*-test for paired samples. In the case of non-normally distributed values, we will apply Wilcoxon's signed-rank test. Commercially available software (PASW for Windows, version 18.0; SPSS, Munich, Germany) will be used for all statistical computing.

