As a precursor of dental caries, initial subsurface lesions appear in many patients [1]. These lesions were simulated in the present study by the artificial demineralization (*i.e*., subsurface lesion) of half of the enamel specimens before *in situ *incorporation. Furthermore, an investigation of the remineralization processes requires the utilization of artificially demineralized enamel specimens that are adjacent to sound specimens. Due to the possibility of disintegration during the *in situ *exposure, the dentin specimens were not artificially demineralized. Four specimens that were obtained from one bovine tooth were embedded into the removable denture of one patient during each experimental phase (Figures 3a and 4). This procedure ensured that the specimens from one tooth were only used for one patient and that one bovine individual-to-one patient regimen was maintained. Furthermore, the enamel and dentin specimens correlated with respect to their source during each test phase, and this permitted a comparison of the *in situ *effects of demineralization and remineralization between dentin and enamel.

To investigate the effects of the study medication on the specimen surfaces after a wearing period of five and seven weeks, the surfaces were divided as described (Figure 3). By covering the respective surface areas with acid-resistant nail varnish and a flowable composite, the sound and artificially demineralized regions were maintained during the entire *in situ *investigation for the microradiographic analyses. Additionally, the coverage of the effect fields (E1; Figure 3) after five weeks ensured that this surface areas were not affected by additional de- and remineralizing effects. This method allowed the determination of distinguishable test areas.

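### In the pre-demineralised enamel, the measured starting lesion is used only by subtraction although SN and G are tested on different teeth; adjusting for it could recover precision

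*Protocol article*

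**What the plan says.** **Specimens per tooth** (Protocol article, Specimen preparation and lesion formation). Two enamel specimens "were prepared from the labial aspect of each crown", and for dentin: "Two dentin specimens were prepared from the cervical regions: one specimen from the oral and one from the buccal aspect". Artificial lesions are made in half of the enamel specimens, one per tooth.

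**Specimens per phase** (Discussion). "Four specimens that were obtained from one bovine tooth were embedded into the removable denture of one patient during each experimental phase". The reason given for this matching is that dentin and enamel can be compared within a phase.

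**Outcome** (Microradiographic analysis). "Mineral losses in sound areas (ΔZ_Sound_; S in Figure 3) were subtracted from the respective values determined for artificially demineralized areas", and likewise from the exposed fields. For pre-demineralised enamel the change is ΔΔZ = ΔZ_Demin − ΔZ_Effect, computed separately for the five-week and seven-week fields. Lesion depth is handled in the same way.

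**Test and sample size** (Statistical analyses). The comparison is by a t-"test for paired samples. In the case of non-normally distributed values", Wilcoxon's signed-rank test replaces it. No covariate is named. The planning inputs are "adequate power of 80% and a defined significance level of 5% (p < 0.05") and "The expected mean value of mineral loss was 200 vol% × μm with a standard deviation of 400 vol% × μm"; "the number of participants was determined to be 38 (in anticipation of a dropout rate of 10"%).

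**The concern.** The crossover pairs SN and G within a patient but not within a tooth. In the pre-demineralised enamel, the two specimens entering a patient's SN-G difference can begin with lesions of different size. Subtracting the D field removes the additive part of that difference. It is fully efficient only if the change is unrelated to the measured starting value.

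There are two reasons to expect some relation. How much mineral a lesion can gain or lose may depend on its size, although the article does not say so. And the D field is itself a measurement: its error enters ΔΔZ at full weight and also enters the measured starting value, which ties the two together even if the true lesions were all alike.

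At stake is precision in a small trial, and a chance difference in starting lesions between treatments that the estimate does not take into account.

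**Working it through.** **1. Two teeth per patient.** Specimens per tooth: 2 enamel + 2 dentin = 4. Specimens worn per phase: 4, all from one tooth. Specimens are removed at the end of a phase and new ones are fitted for the next, so two phases need 2 × 4 / 4 = 2 teeth per patient, or 38 × 2 = 76 in all; 155 were obtained. Within each patient, SN and G are thus tested on different teeth.

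**2. The plan's own sample size.** Standardised effect 200/400 = 0.5. A paired t-test at two-sided 5% (sidedness is not stated) needs n = 34 for 80% power, with actual power 80.8%. Allowing for dropout, 34/0.9 = 37.8, rounded up to 38. The stated figure reproduces if 400 is the SD of the paired difference.

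**3. What subtraction leaves.** If change has slope b on the starting ΔZ, a share b² of the starting-lesion variance stays in the change score: 0% at b = 0, 1% at b = 0.1, 9% at b = 0.3, 25% at b = 0.5. The article gives neither b nor the SD of the starting lesions.

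**4. Possible gain from adjustment.** Assume that 400 is the SD of the SN-G difference in ΔΔZ, and let r be its correlation with the SN-G difference in D-field value. The residual SD is 400 × √(1 − r²). Power at 34 completers uses the noncentral t with 34 − 2 = 32 degrees of freedom. The intercept also carries the error of the estimated slope, which on average multiplies its variance by about 1 + 1/(34 − 3) = 1.032; the last column includes this.

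| r (assumed) | Residual SD | Power, slope taken as known | Power, slope error included |
|---|---|---|---|
| no adjustment | 400 | 81% | – |
| 0.1 | 398 | 81% | 80% |
| 0.3 | 382 | 84% | 83% |
| 0.5 | 346 | 90% | 89% |

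On variance alone, adjustment pays when (1 − r²) × 1.032 < 1, that is, when r exceeds about 0.18. Below that it costs about one point of power at most.

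**5. The covariate must not be centred at its sample mean.** With the raw SN-G difference in D-field value as covariate, the intercept is the treatment difference at equal starting lesions. Centred at the sample mean, the intercept is again the unadjusted mean difference, but tested against a standard error that is too small. In 200,000 simulated trials of 34 pairs with r = 0.5 and no treatment effect, the uncentred test rejected in 5.0% and the centred one in 8.7%.

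**The case against.** The strongest reply is that nothing here is wrong. A paired test on within-specimen change is valid, the sample size reproduces, and covariate adjustment is an option that an unseen analysis plan could add. The article also limits tooth noise in several ways: sound-field subtraction, change taken within the specimen, one 19-day immersion at controlled pH, one bovine individual kept to one patient (so a patient's two incisors may come from one animal), and a between-tooth spread described as small. The SD of 400, based on in vitro studies, may already contain tooth variation.

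Most of this stands. It limits the point to efficiency and leaves the gain possibly near zero. It does not remove the point, because the article does fix the change score and the tests, and neither test takes a covariate. Uniform true lesions would not settle it either: the more alike they are, the more the D-field difference is measurement error, which subtraction passes on in full.

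A reader might infer more, without support in the document:

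- **Bias.** Nothing suggests that teeth were assigned according to treatment, and allocation is blinded. Chance differences between teeth are already reflected in the paired SD.
- **All specimens start from different lesions.** Sound enamel and dentin carry no artificial lesion and are referenced to their own covered field. Only tooth susceptibility can differ there, and the D-field covariate does not address it.
- **Dentin should be split across the two teeth.** That would break the same-tooth comparison of dentin and enamel which the Discussion gives as a purpose of the matching, and would change the design after 14 patients have completed both phases. Any figure for its benefit needs a between-tooth variance that the article does not give.

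**Conclusion.** The point holds as a minor efficiency recommendation, for the pre-demineralised enamel only. That the two phases use different teeth follows from the specimen counts. That the starting value enters only by subtraction follows from the stated outcome and tests. The planned analysis remains valid and unbiased.

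The size is conditional on two assumptions: that the planning SD applies to this paired difference, which the article does not say, and the value of r, which it does not give. On these, the effect on power runs from nothing, or a loss of about one point, at r = 0.1 to a gain of eight or nine points at r = 0.5.

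**What to change.** Before unblinding, prespecify for the pre-demineralised enamel, for ΔΔZ and for lesion-depth change, at five and at seven weeks:

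1. For each patient, form the SN-G difference in change and the SN-G difference in the matching D-field value (ΔZ_Demin, or lesion depth in the D field).
2. Regress the first on the second with the covariate uncentred, so that zero means equal starting lesions. Test the intercept and report it with its confidence interval.
3. Keep the unadjusted paired t-test, or the Wilcoxon test where normality fails, as a sensitivity analysis.

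The cost is one degree of freedom and a small loss if r turns out close to zero. The D field is already measured in every such specimen, and the article says that evaluation waits for the last participant with allocation still blinded, so the change can be made cleanly. Sample size, specimen allocation and the analyses of sound enamel and dentin stay as they are.
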